#### Definition of analyses population {20}

The primary analysis will be conducted according to the intention-to-treat (ITT) principle [46, 47].

We define the ITT population as all admitted patients suspected of LRTI who sign informed consent and subsequently are allocate to one of two sputum collection groups. Sputum samples obtained by tracheal suction from patients in the intervention group, who are not able to expectorate, will be analyzed separately from the ITT analyses.

The primary analysis compares the tracheal suction group and the expiratory technique group to identify the most effective method for obtaining good quality sputum samples. The secondary analysis consists of an agreement analysis [48] between forced expiratory technique alone and forced expiratory technique after sputum induction.

Additionally, analysis of the secondary outcome of adverse effects will be conducted at baseline (right after allocation) and at the latest, 10 min. after the intervention. Clinical symptoms (cough, expectoration, chest pain, or dyspnea), SaO_2_, RR, and CR10 Borg scale [40] will be measured. Furthermore, a 5-point Likert scale will be used to measure patient experience of the procedure. The analyses will be adjusted for variables with a large influence on the outcome, which is an odds ratio larger than 2, to accommodate bias [49].

Descriptive analyses will be performed on the pathogens found when the specimens are cultured according to differential quality criteria.

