### Baseline variables {25}

Demographics, symptoms, and smoking are collected from a patient interview. Vital parameters, comorbidities, suspicion of pneumonia, diagnostic packages [33], severe acute respiratory syndrome coronavirus 2 (SARS-CoV-2), disease severity assessment (CURB-65 [34], PSI [35], and Danish Emergency Process Triage (DEPT) [36]), blood tests (C-reactive protein, leucocytes, neutrophils) length of hospital stay, antibiotic consumption, and inhaled medicine are extracted from the patient’s medical record (Table 1).

**Table 1 Tab1:** Demographic and baseline clinical characteristics

Variable	Overall	Group 1 total (*n* =)	Group 2 total (*n* =)
		Tracheal suction (*n* =)	Forced expiratory technique (*n* =), induced sputum (n =)
Site			
Aabenraa			
Sønderborg			
Sex, *n* (%)			
Age, mean (SD)			
Smoking status			
Current smokers, *n* (%)			
Ex-smokers, *n* (%)			
Non-smokers, *n* (%)			
Symptoms			
Cough, *n* (%)			
Expectoration, *n* (%)			
Chest tightness, *n* (%)			
Dyspnea, *n* (%)			
Severity assessment			
CURB-65 score* 0–1, *n* (%)			
CURB-65 score* 2, *n* (%)			
CURB-65 score* 3–5, *n* (%)			
PSI* risk class 2–3, *n* (%)			
PSI* risk class 4, *n* (%)			
PSI* risk class 5, n (%)			
Triage level 1, *n* (%)			
Triage level 2–3, *n* (%)			
Triage level 4–5, *n* (%)			
Diagnostic packages			
Airways symptoms, *n* (%)			
Fever, *n* (%)			
Dyspnea, *n* (%)			
Unspecific illness, *n* (%)			
Suspicion of COVID-19 infection, *n* (%)			
Other, *n* (%)			
Suspicion of pneumonia, *n* (%)			
SARS-COV-2 positive at admission, *n* (%)			
Comorbidities			
COPD*, *n* (%)			
Asthma, *n* (%)			
DM*, *n* (%)			
CVD*, *n* (%)			
Cancer, *n* (%)			
Other, *n* (%)			
Vital parameters			
SaO_2_*, mean (SD)			
RR*, median (IQR)			
HR*, median (IQR)			
Systolic blood pressure, median (IQR)			
Diastolic blood pressure, median (IQR)			
Fever > 38 °C, *n* (%)			
Altered mental status, *n* (%)			
Blood tests			
C-reactive protein, mean (SD)			
Leucocytes, mean (SD)			
Neutrophils, mean (SD)			
Did the patient receive antibiotic treatment			
Within 1 month, *n* (%)			
Before sputum collection, *n* (%)			
Inhaled medications, *n* (%)			
Length of hospital stay, mean (SD)			

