### Co-variables

Co-variables (listed and defined below) will be measured and compared between the two allocation groups. Patients’ symptoms, oxygen saturation, respiratory rate, and overall experience will be measured before (right after allocation) and after sputum collection (measured at the latest 10 min after the procedure). Side effects observed by the project assistants and experience by the patient during the procedure will be registered once after sputum collection. Data on mortality and re-admission will be extracted from the patient medical record. The projects assistants will follow standardized protocols to register all the co-variables including the questions concerning patient experiences.

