## Statistical method

### Sample size consideration {11}

It is hypothesized that the intervention group receiving expiratory techniques is non-inferior to the tracheal suction group. Grouping two methods in the intervention arm, there will be fewer missing values and only two comparison groups.

Based on clinical practice and literature, it is assumed that no sample will be obtained from 50% of patients by forced expiratory technique alone [9, 10, 42], 30% from patients by sputum induction combined with the forced expiratory technique [23, 43], and 10% from patients using tracheal suction [28]. The proportion of obtained samples classified as good quality is assumed to be 75% for the procedures using expiratory techniques [23, 27, 43] and 90% for tracheal suction [28].

Considering these assumptions, the study’s power is 84% with 260 patients, including missing values. The power of the study was calculated with a Monte Carlo simulation using logistic regression.

An internal register showed that at least 1250 patients were admitted to the study ED with suspicion of infection annually, and of these, 600 patients were diagnosed with pneumonia. Including 260 patients with suspected LRTI will take five months, taking into account exclusion criteria, weekends/holidays, and missing data.

To avoid overfitting in the primary analysis, we followed the relaxed one in ten rule for the fixed effects and one in 20 rule for the random effects [44].

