### Statistical analysis {27}

#### Descriptive statistics

Descriptive statistics will be utilized to assess if exchangeability is fulfilled for baseline variables. For categorical variables, Fischer’s exact test or chi-square test will be used to test if the distribution between the two groups is different. For discrete and continuous variables, the Wilcoxon rank-sum test or Student *t*-test will be utilized to assess if the distribution is similar between the two groups depending on normal data distribution.

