#### Analysis for primary outcome

For the primary outcome, the following analyses will be utilized:
To assess the suitability of the sputum sample between the two collecting methods groups, a hierarchical mixed effect logistic model with and without imputed values will be utilized to accommodate the random effect’s hierarchical structure, which manifests according to different personnel collecting the samples and geographical variation (Table 2).

**Table 2 Tab2:** Results of the primary outcome regarding specimens’ suitability and secondary outcome of adverse effects and patient experience. Tracheal suction method (reference group) compared to expiratory technique methods

Outcome	Unadjusted OR (CI) ***P***	Adjusted OR (CI) ***P***

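### The only covariate rule, adjust for variables with an odds ratio above 2, depends on coding and units and leaves the adjusted estimates not pre-specified

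*SAP article*

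**What the plan says.** The rule stands in Definition of analyses population {20}: "The analyses will be adjusted for variables with a large influence on the outcome, which is an odds ratio larger than 2". The stated purpose is to deal with bias, and a source is cited. The section lists no candidate variables and gives no unit, reference level or screening model. It does not mention odds ratios below 0.5.

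Under Analysis for primary outcome, "a hierarchical mixed effect logistic model with and without imputed values will be utilized", with random effects for personnel and geography. No fixed-effect covariate is named. Table 2 has an unadjusted column and one headed "Adjusted OR (CI" for specimen quality and adverse effects, and unadjusted and adjusted coefficients for patient experience. The text does not say which column decides the trial. Adverse events are to be analysed with a mixed-effects Poisson model.

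Two sections supply variables that could be screened:
- Baseline variables {25} says that "length of hospital stay, antibiotic consumption, and inhaled medicine are extracted" from the medical record, and Table 1 has the row "Length of hospital stay, mean (SD").
- Co-variables uses that word for measures that include those taken "after sputum collection (measured at the latest 10 min after the procedure"), as well as mortality and re-admission.

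Sample size consideration {11} adds, for the primary analysis, that "we followed the relaxed one in ten rule for the fixed effects". The Abstract and the Discussion both give avoidance of data-driven analysis as a purpose of the SAP.

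**The concern.** A numerical threshold looks like pre-specification, but here it fixes the cut-off and not the covariates. Which variables pass depends on which category is the reference, on the unit of each continuous variable, on whether the modelled event is a suitable or an unsuitable specimen, and on the play of chance. Two analysts following the text could report different adjusted odds ratios from the same data, and both would comply.

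For the adverse-event count the rule has no direct reading, because a Poisson model yields rate ratios. The rule also contains no time restriction, so a variable affected by the allocated procedure is not barred from the adjusted model. The adjusted column of Table 2 is at stake, and so is the unstated choice between it and the unadjusted column.

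**Working it through.** The plan gives no figure for this rule. The checks use the rates and sample size in Sample size consideration {11}. Covariate effects and prevalences are assumptions.

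**Inputs.** 260 patients allocated 1:1, so 130 per arm. No sample from 10% with tracheal suction. For the intervention arm, no sample from 30%, or from 50% x 30% = 15% if the two steps are read as sequential. Good quality 90% with suction and 75% with expiratory techniques.

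These inputs come close to the plan's own power of 84%. A two-sided 5% comparison of 90% with 75% gives 81.7% on 117 and 91 samples and 85.1% on 117 and 110.5. The stated figure lies between, so the inputs are read plausibly.

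**1. Coding.** The inverse of 3 is 0.33. A factor with odds ratio 3 passes; with the reference level swapped, it fails. In simulation at 30% prevalence, a true odds ratio of 3 is kept in about 76-87% of trials, depending on outcome direction and continuity correction. The same effect coded as 1/3 is kept in effectively none.

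**2. Units.** Age at 1.05 per year fails. Over 10 years it is 1.05^10 = 1.63, which also fails. Over 30 years it is 1.05^30 = 4.32, which passes. The data and the fit are the same each time.

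**3. Room in the primary model.** Expected unsuitable specimens:
- suction: 130 x 0.90 x 0.10 = 11.7
- expiratory: 130 x 0.70 x 0.25 = 22.75, or 130 x 0.85 x 0.25 = 27.6
- total: 34.5 or 39.3

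One in ten allows 3.4 to 3.9, that is about 3 fixed effects including allocation. The plan does not say which variables are kept if more than that pass.

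**4. Chance selection.** Simulated frequency with which a binary variable unrelated to the outcome shows a sample odds ratio above 2, with 208 or 227 specimens:

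| Assumed prevalence | Passes |
|---|---|
| 5% | about 16-28% |
| 10% | about 9-19% |
| 30-50% | about 3-7% |

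The ranges reflect the number of specimens, whether the event is a suitable or an unsuitable specimen, and whether 0.5 is added to each cell. The plan fixes neither of the last two. A noise variable observed before allocation mainly costs precision; it does not bias the comparison.

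**5. A variable affected by allocation.** Hypothetical case: a binary variable has prevalence 30% with suction and 60% with expiratory techniques. It multiplies the odds of a good specimen by 1/3 from a base of 90% (odds 9, falling to 3, or 75%). Allocation has no other effect.
- suction: 0.3 x 0.75 + 0.7 x 0.90 = 0.855
- expiratory: 0.6 x 0.75 + 0.4 x 0.90 = 0.810
- total odds ratio: (0.810/0.190) / (0.855/0.145) = 0.72

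With 50% in place of 60% it is (0.825/0.175) / (0.855/0.145) = 0.80. Adjusted for the variable it is 1.00, so a real difference disappears. Coded as absence, this variable has odds ratio 3 and passes the rule.

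**The case against.** Several points on the other side have force.

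- **Scope.** The sentence closes a paragraph on secondary outcomes, and the primary model names no covariates. Extension to the primary outcome is an inference from the adjusted odds ratio for specimen quality in Table 2. It is a fair inference: without it, that column has no covariate rule at all, and the rule would apply only to a count and an ordinal score, where an odds-ratio threshold fits worst.
- **Prior knowledge.** The threshold might refer to effects known from earlier work. The text does not say so and lists no variables, so the covariate set is open on either reading.
- **Length of stay.** A reader might infer that the plan intends to adjust for it. The document does not support that. Nothing makes Table 1 the candidate pool, and as a continuous variable per day, length of stay would hardly reach an odds ratio of 2. What stands is that no sentence limits candidates to pre-randomisation variables.
- **One in ten.** A reader might see a conflict between the threshold and this limit. A threshold and a cap can operate together. What is missing is an order of entry when too many variables pass.
- **Noise count.** It is tempting to multiply the chance rates by the rows of Table 1. Many rows are levels of one variable, and the prevalences are unknown, so no such count is supported.
- **Unadjusted results.** They are also reported, so one comparison without selected covariates remains. That limits the harm but does not say which column counts.

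**Conclusion.** The concern holds for the rule as written: it is one-sided, depends on units, is undefined for the Poisson model, and selects covariates by their association with the outcome. The adjusted estimates in Table 2 are therefore not pre-specified, contrary to the SAP's stated aim. The coding and unit defects follow from the rule itself and need no assumption about the data. The chance rates (about 3-7% per variable at 30-50% prevalence, 9-19% at 10%) rest on assumed prevalences and on the plan's own quality and missing-sample rates.

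Entry of a post-randomisation variable is something the text permits, not something it states as intended. The documents do not show that the treatment estimate will be biased. The point deserves correction because the remedy is simple. It does not bear on the sample size.

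**What to change.** Delete the odds-ratio screen. Name one short, fixed set of covariates recorded before allocation for all adjusted analyses, each with its coding and unit. Site, age (for example linear, per 10 years) and COPD (yes or no) would serve, and all are already collected.

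Keep the primary model within the one-in-ten limit. If geography stays a random effect as planned, allocation, age and COPD make three fixed effects. If site is entered as a fixed effect, one of the others has to go.

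Baseline symptoms are less suitable. Co-variables places their first measurement right after allocation, the project assistants are unblinded, and symptoms such as expectoration are part of the adverse-event outcome.

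State whether the adjusted or the unadjusted estimate is primary. State that length of stay and every measure taken after allocation are excluded from adjustment.

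The cost is SAP wording only, with no new data and no change in sample size. The downside is that a strong predictor not named in advance is not adjusted for.

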### Statistical analysis {27}

#### Descriptive statistics

Descriptive statistics will be utilized to assess if exchangeability is fulfilled for baseline variables. For categorical variables, Fischer’s exact test or chi-square test will be used to test if the distribution between the two groups is different. For discrete and continuous variables, the Wilcoxon rank-sum test or Student *t*-test will be utilized to assess if the distribution is similar between the two groups depending on normal data distribution.

#### Analysis for primary outcome

For the primary outcome, the following analyses will be utilized:
To assess the suitability of the sputum sample between the two collecting methods groups, a hierarchical mixed effect logistic model with and without imputed values will be utilized to accommodate the random effect’s hierarchical structure, which manifests according to different personnel collecting the samples and geographical variation (Table 2).

**Table 2 Tab2:** Results of the primary outcome regarding specimens’ suitability and secondary outcome of adverse effects and patient experience. Tracheal suction method (reference group) compared to expiratory technique methods

Outcome	Unadjusted OR (CI) ***P***	Adjusted OR (CI) ***P***

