### Study design and setting {9}

The study design is a pragmatic, non-inferiority, randomized controlled trial (RCT). The trial is conducted from the 9th of November 2020 until the 1st of July 2021 at the University Hospital of Southern Denmark including the hospitals of Aabenraa and Sønderborg with a hospital coverage of approximately 250,000 inhabitants. The standard method for sputum collection at both EDs is tracheal suction.

Six project assistants from the ED (experienced nurses and physiotherapist) will identify eligible patients and collect informed consent (Additional file 5) and data. The project assistants will receive bedside and simulation training in all the included sample methods on how to obtain an optimal specimen. Furthermore, a guideline on how to perform the expiratory technique will be developed to support consistent data collection.

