**Patient symptoms**			
Cough			
Dyspnea			
Expectoration			
Chest tightness			

^**a**^*SaO*_*2*_, oxygen saturation; *RR*, respiratory rateFor the procedure experience using a five-point Likert scale, a Wilcoxon rank test will be performed to compare the two allocation groups according to sample methods.

Model control for the generalized linear mixed models will consist of assessing the deviance residuals’ normality assumptions for each center by way of quantile-quantile plots. To assess if the variables in the descriptive analysis are normally distributed, quantile-quantile plots will be utilized.

If any of the generalized linear mixed models do not converge, a simplification of the covariance structure will be utilized.

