## Adherence and protocol deviations {19}

### Adjustments after the study start and before recruitment completion

Due to the SARS-CoV-2 pandemic, patient distribution was altered, and it was necessary to extend the recruitment to include the second site. The study period was adjusted with study start from October 19th to November 9th, and study completion from March 1st to July 5th and will include at least 260 participants. New sample size and power calculations were performed where the clinical significant absolute difference was set at 15% points. The personnel conducting the sample size calculations do not know the participants’ outcomes.

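### Hospital enters the primary and adverse-event models as a random effect with only two levels; a fixed site term would be sounder (minor)

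*SAP article*

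**What the plan says.** Under 'Analysis for primary outcome', the SAP states that "a hierarchical mixed effect logistic model with and without imputed values will be utilized", with random effects arising from "different personnel collecting the samples and geographical variation". 'Analysis for secondary outcomes' repeats this structure for the Poisson model of adverse events.

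'Study design and setting {9}' describes the trial as "including the hospitals of Aabenraa and Sønderborg", with "Six project assistants from the ED" enrolling patients and collecting data. The second hospital came late: under 'Adjustments after the study start and before recruitment completion', "it was necessary to extend the recruitment to include the second site". 'Randomization {10}' specifies 1:1 allocation in blocks of six, unstratified. Residuals are to be checked centre by centre. Site is listed in baseline Table 1, but no section makes it a fixed effect.

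For model size, 'Sample size consideration {11}' cites a "one in 20 rule for the random effects". The only fallback stands after Table 5. It covers any generalized linear mixed model and applies if the models "do not converge, a simplification of the covariance structure will be utilized".

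**The concern.** A random effect treats the hospitals as draws from a population and estimates the spread of that population. With two hospitals the spread rests on one degree of freedom, and recruiting more patients does not change that. Maximum likelihood often puts such a variance at exactly zero. The fitted model is then the one without site, although the report would describe a model that accounts for it.

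A zero variance can be a converged fit, so the stated fallback need not apply. Where it does apply, it does not say which term goes. The plan describes no random slopes, so simplifying would mean removing an intercept, and that could be the hospital's. The choice would be made with the data in hand, in a trial that was not stratified by site and gained its second site after it started.

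**Working it through.** **Inputs.** From 'Sample size consideration {11}': 260 patients, 90% good quality with tracheal suction and 75% with expiratory techniques, no sample from 10% and 30%. With 130 per arm, the samples obtained are 130 × 0.90 = 117 and 130 × 0.70 = 91, in total 208. The planned treatment log odds ratio is ln(0.75/0.25) − ln(0.90/0.10) = ln 3 − ln 9 = −1.10. The SAP gives no site difference, site split or assistant variance, so these are varied.

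**The plan's own figure.** The SAP states 84% power from a simulation with logistic regression. Repeating it without clustering, as a two-sided 0.05 test of a difference, gives 82.3% with 30% missing in the expiratory arm and 85.8% with 15% missing (0.5 × 0.3). The inputs are therefore close to those the plan used.

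**Closed form, two equal sites.** Let d be the estimated site log odds ratio and SE its standard error. The variance estimate is zero when (d/SE)² < 2 under maximum likelihood, or < 1 under REML. With no true site difference:
- ML: P(χ²₁ < 2) = 84%
- REML: P(χ²₁ < 1) = 68%

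With the plan's figures, the information is 117 × 0.90 × 0.10 + 91 × 0.75 × 0.25 = 10.53 + 17.06 = 27.59, or 13.80 per site. So SE = √(2/13.80) = 0.381. The ML estimate is zero whenever |d| < 1.414 × 0.381 = 0.538, that is, when the observed site odds ratio lies between about 0.58 and 1.71. For a true site log odds ratio δ,

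P(zero) = Φ((0.538 − δ)/0.381) − Φ((−0.538 − δ)/0.381).

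**Simulation.** A random-intercept logistic model with site only was fitted by ML to 260 patients, 400 runs per setting, sites 50:50:

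| True site OR | δ | P(zero), formula | P(zero), simulated | Shift in treatment log OR if site is left out, 95th percentile |
|---|---|---|---|---|
| 1.28 | 0.25 | 76% | 76% | 0.07 |
| 1.65 | 0.50 | 54% | 58% | 0.10 |
| 2.12 | 0.75 | 29% | 30% | 0.14 |
| 2.72 | 1.00 | 11% | 13% | 0.18 |
| 4.48 | 1.50 | 1% | 1% | 0.28 |

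Other settings:
- **Site effects drawn at random**, SD 0 / 0.2 / 0.4 on the logit scale: zero in 86% / 74% / 59% with sites 50:50, and in 90% / 83% / 64% with sites 75:25. At SD 1.0 it is still zero in 30% and 40%, because two hospitals drawn from a wide distribution can happen to be alike.
- **Three-level model**, three assistants nested in each site, 150 runs: with assistant SD 0.4, zero in 85%, 65% and 51% at site SD 0, 0.4 and 0.8.
- **Separate check**, 208 samples, sites 65:35, 60 runs per setting and so rougher: zero in 95%, 65%, 12% and 0% at site ORs of 1, 1.65, 2.7 and 4.5.

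**Effect on the treatment estimate.** Random against fixed site differs by a median of 0.01 to 0.02 and a 95th percentile of 0.04 to 0.07 in every completed setting. In the separate check, leaving site out at ORs of 2.7 and 4.5 moved the log odds ratio by up to 0.15 to 0.27 (95th percentile) and changed about 5% of significance calls. With assistants nested in sites and their intercepts kept, dropping site moved it by only 0.06 to 0.10 (95th percentile) at site ORs from 1 to 4.5.

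**The case against.** The best defence is that the adjustment tends to vanish when there is little to adjust for. A zero estimate is common only when the hospitals are alike. When they differ clearly, the random effect is picked up and the treatment estimate is almost that of a fixed-site model. Against a planned log odds ratio of about −1.1, a shift of 0.07 is negligible. This stands, and it is why the point is minor.

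A reader might infer that the primary model will in general fail to adjust for site. The calculations do not support that without the condition on site difference. Assistant intercepts may also absorb much of a site difference if each assistant works at one hospital, but the SAP does not say whether they do.

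A reader might also infer that the random site term is the only protection against a chance imbalance between hospitals. That goes too far. Site is in Table 1, baseline variables are compared between arms, Table 2 has an adjusted odds ratio, and 'Definition of analyses population {20}' adjusts for variables with an odds ratio above 2. This cover is partial: the rule does not name site, depends on the data and stands in a paragraph on secondary outcomes.

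Nor do the documents or calculations show that the models will often fail to converge. Zero variances were counted, and these can be valid, converged fits.

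**Conclusion.** The point holds as a minor one. Two hospitals are too few to estimate a between-hospital variance. With a site odds ratio up to about 1.65, or an SD up to about 0.4, the estimate is zero in roughly 60% to 95% of trials. With a site odds ratio of about 2.7 or more it is seldom zero. Either way the treatment log odds ratio stays within about 0.07 (95th percentile) of a fixed-site analysis, so the planned model as such is no threat to the primary conclusion.

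The open-ended fallback is the larger exposure. If it removes site while the hospitals differ by an odds ratio of 2.7 to 4.5, the shift is about 0.15 to 0.28 (95th percentile), and less if assistant intercepts absorb the difference. How often the fallback would be needed is unknown.

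This rests on reading geography as hospital and on assumed site splits and differences. The simulations cover the logistic model. For the Poisson model the argument is the same two-level one, without figures.

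**What to change.** In the logistic and Poisson models, enter site as a fixed effect (one parameter) and keep project assistant as the only random intercept. Replace the general fallback with one named model: if the mixed model does not converge, use fixed site with no random effect. Offering assistant-clustered standard errors as an alternative would leave a choice open, and six clusters are too few for them to be reliable.

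The cost is SAP wording and one degree of freedom. On the plan's assumptions, about 117 × 0.10 + 91 × 0.25 = 34 samples are unsuitable. A one-in-ten count therefore allows about three fixed parameters, and treatment plus site uses two.

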### Outcome definitions {26}

*Primary outcome*. The quality of sputum samples, binary outcome*Secondary outcome 1*. Number of adverse events, discrete outcome
Aggravation of SaO_2_ and SaO_2_ ≤ 93% (COPD patients ≤ 88%), binaryAggravation of RR and RR lower than 12 or higher than 20 times per minute, binaryOccurrence or aggravation of symptoms (cough, expectoration, dyspnea, chest pain), binaryAggravation of patient symptoms experience, binaryOccurrence of side effects observed by the project assistant, binaryDeath within 7 days from admission, binary30 days re-admission after current hospitalization, binary*Secondary outcome 2*. Patient experience of the sputum collection procedure, ordinal outcome

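### The primary outcome is given both an unadjusted and an adjusted odds ratio with p-values, the plan does not say which decides, and the adjusted one is not fixed in advance

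*SAP article*

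**What the plan says.** Outcome definitions {26} lists one primary outcome: "The quality of sputum samples, binary outcome". For its analysis, Analysis for primary outcome states that "a hierarchical mixed effect logistic model with and without imputed values will be utilized". It names random effects for the personnel collecting samples and for geography, but no covariates. Table 2 in the same section then gives specimen quality two results under "Outcome Unadjusted OR (CI) *P* Adjusted OR (CI) *P", and neither column is marked as primary.

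Three other places bear on the choice:

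- Sample size consideration {11}: "To avoid overfitting in the primary analysis, we followed the relaxed one in ten rule for the fixed effects".
- Definition of analyses population {20}: "The primary analysis compares the tracheal suction group and the expiratory technique group to identify the most effective method".
- The same section, closing a paragraph that opens with the secondary outcome of adverse effects: "The analyses will be adjusted for variables with a large influence on the outcome, which is an odds ratio larger than 2".

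Confidence interval and p-value {16+17+18} sets significance at p below 0.05. It waives any multiplicity adjustment on the ground that there is only one primary outcome.

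**The concern.** One primary outcome does not amount to one primary result. Two p-values are planned for it, each read against 0.05, and the reason given for waiving multiplicity adjustment does not cover two estimates of the same outcome. If they fall on opposite sides of 0.05, the plan does not say what the trial has shown.

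The adjusted column has a further weakness. Its covariates come from an odds-ratio threshold, with no named list and no statement of whether the threshold applies to the trial's own data or to earlier knowledge. Different analysts could follow the rule and report different adjusted results.

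The SAP says that it exists to prevent reporting bias and data-driven analysis, and this gap leaves room for both at the main result.

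**Working it through.** **1. The plan's own figure.** Inputs from Sample size consideration {11}: 260 patients (130 per arm at 1:1), good quality in 90% with suction and 75% with expiratory techniques, and no sample in 10% with suction. For the expiratory arm the section gives 50% with no sample by forced expiration alone and 30% with induction. Read in sequence, that is 0.5 × 0.3 = 15%.

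- Samples: 130 × 0.90 = 117 and 130 × 0.85 = 110.5.
- Log OR = ln(0.75/0.25) − ln(0.90/0.10) = ln 3 − ln 9 = −1.099, so OR = 1/3.
- SE = √[1/(117 × 0.9 × 0.1) + 1/(110.5 × 0.75 × 0.25)] = √(0.0950 + 0.0483) = 0.378.
- Power = Φ(1.099/0.378 − 1.96) = Φ(0.94) ≈ 82.7%. A pooled two-proportion test gives 85.1%.

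The stated 84% lies between these two. If 30% of the expiratory arm has no sample (130 × 0.70 = 91 samples), the figures are 80.1% and 81.7%. The stated power thus reproduces as a two-sided difference test without covariates. This does not prove that the unadjusted result was meant to decide, because the section says only that logistic regression was simulated.

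**2. The passages side by side.** The overfitting remark about fixed effects makes most sense for an adjusted primary model. The description of the primary analysis as a comparison of two groups fits either column. The adjustment sentence may or may not reach the primary outcome. The model text and Table 2 do not choose. No passage ranks the two results.

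**3. The columns are different quantities.** Illustration with assumed strata of equal size and a covariate with OR 3:

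- Stratum A: 90% with suction, 75% with expiratory; OR = 3/9 = 1/3.
- Stratum B: 75% with suction, 50% with expiratory; OR = 1/3.
- Combined: 82.5% and 62.5%; odds 4.714 and 1.667; OR = 1.667/4.714 = 0.354.

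The adjusted OR is 0.333 and the unadjusted OR is 0.354, with perfect balance between arms. The average of the stratum risk differences, (15 + 25)/2 = 20 points, equals the combined difference, 82.5 − 62.5 = 20. The gap belongs to the odds-ratio scale. With no arm effect both odds ratios are 1.

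**4. Size with no true difference.** Simulated logistic models, 117 against 91 samples, 82.5% good quality, two-sided 0.05, 4,000 trials per row, no random effects. The document gives no covariate effects, so these are assumed (binary, 40% prevalence).

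| Covariates | Unadjusted | Adjusted | Either | Verdicts conflict |
|---|---|---|---|---|
| 2, OR 2 | 4.0% | 4.8% | 5.4% | 1.9% |
| 4, OR 2 | 4.5% | 4.9% | 5.9% | 2.3% |
| 4, OR 3 | 4.5% | 5.2% | 6.8% | 4.0% |
| 6, OR 2.5 | 4.7% | 5.5% | 7.1% | 4.0% |
| 10, OR 1.5, kept if observed OR above 2 | 4.0% | 4.5% | 5.2% | 2.0% |

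At the plan's 90%, with three covariates of OR 1.5 to 2.2, the either-column rate is 5.1–5.3% and conflicts occur in 1.4–2.1%. Over all assumptions tried, the either-column rate is roughly 4–7%. Two independent tests would give 1 − 0.95² = 9.75%. The two estimates are highly correlated, so that bound is not approached.

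**5. Size at a true OR of 1/3.** With three covariates of OR about 2.2 and about 85% good quality with suction, rejection was 86.0% unadjusted and 89.7% adjusted (complete cases). The two verdicts conflicted in 5.6% of trials. Further runs put the conflict at about 5–7% and the power gain from adjustment at about 2–4 points. With suction at 90%, the conflict ranged from 3.5% (covariate OR 1.5) to 6.2% (OR 2.2).

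**The case against.** The best reply is that the fixed-effects remark and the adjustment sentence together make the adjusted model primary, with the unadjusted column shown for reference. That is the likelier intention. It is not stated, and even if it were, the OR-above-2 rule would leave the deciding model open.

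A reader might also infer that the investigators can pick a verdict unseen. The documents do not support that. Table 2 commits them to publishing both results with intervals and p-values, and the Blinding section keeps the investigator blinded until data analysis is completed. What remains is which result is called the finding when the two disagree.

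A reader might further infer a large error inflation, especially after counting the versions with and without imputation as four results. That count mixes in a separate choice: Missing data {28+29} presents the imputed and complete-case versions as a way to study the influence of missing data. For the two columns alone the inflation is small.

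Finally, the simulations test a difference, whereas the design is non-inferiority. The objection stands as a limit on the percentages: they are not error rates of a non-inferiority claim. It does not remove the gap, since such a claim also needs one designated estimate.

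**Conclusion.** The point holds as a missing designation combined with an open covariate rule. It does not show a seriously inflated error rate. Allowing either column to decide moves the false-positive rate to roughly 4–7%, from about 4–5.5% for one column, and produces conflicting verdicts in about 1–4% of trials with no difference. At a true OR of 1/3, which is the plan's own 90% against 75%, the conflict is about 5–7% with covariate odds ratios near 2, and less with weaker covariates. All these figures rest on assumed covariate effects, models without random effects and a difference test. The conclusion depends on the text, and the figures show only that the consequence is modest but real. It should be corrected before analysis.

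**What to change.** In Analysis for primary outcome, name one decisive estimate: the arm comparison from the mixed logistic model, adjusted for a short fixed list of pre-randomisation variables already collected. Examples are COPD and expectoration at admission. Site should stay in the model's existing geographical term and not be entered a second time as a covariate. State that this list replaces the OR-above-2 rule for the primary outcome.

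Report the estimate as a standardised risk difference with 95% CI. It can then be read against the 15-percentage-point absolute difference given under Adjustments after the study start and before recruitment completion, which the plan does not express as an odds ratio.

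State which missing-data version is primary. Label the unadjusted OR and the other missing-data version as supportive in Table 2, without significance claims of their own.

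The cost is SAP wording and a little more analysis work, because standardising from a mixed model over imputed data takes some extra steps. The unadjusted result can no longer be claimed as primary. In return, adjustment gained about 2–4 points of power under the assumed covariates.
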